The RespiraSense device (PMD Solutions Ltd) was developed to improve the detection of changes in the RR in order to alert staff to out-of-range values that may be clinically significant. In a 48-patient investigation, data were collected to evaluate the difference in RR measurements between the developed RespiraSense device, electrocardiogram (ECG), and direct nursing observations [12]. A clinically relevant agreement between all RR measurements by the 3 different methods was demonstrated. However, few abnormal values were recorded in this investigation, and further research is required to ensure that the device works well to accurately measure the RR at values both higher and lower than the normal range.

**Table 1 table1:** Escalation protocol for the deteriorating patient [8].

Vital sign	Score						
	3	2	1	0	1	2	3
Pulse	≤40	—	41-50	51-90	91-110	111-130	≥131 Unrecordable due to patient condition
Temperature (°C)	≤35	—	35.1-36	36.1-38	38.1-39	≥39	Unrecordable due to patient condition
BP^a^ systolic (mm Hg)	≤90	91-100	101-110	111-219	—	—	≥220 Unrecordable due to patient condition
Respiratory rate (bpm)	≤8	—	9-11	12-20	—	21-24	≥25 or Unrecordable due to patient condition
AVPU^b^	—	—	—	Alert	—	—	Voice pain unresponsive^c^
SaO_2_^d^	≤91	92-93	94-95	≥96 or Unrecordable because patient refused, equipment unavailable, other reason	—	—	Unrecordable due to patient condition
Inspired O_2_	—	—	—	Air	—	Any supplemental O_2_^e^	—

^a^BP: blood pressure.

^b^AVPU: alert, verbal, pain, unresponsive.

^c^If AVPU is V or C due to patient sedation, it will be charted as S and score 0 rather than 3.

^d^SaO_2_: oxygen saturation.

^e^Note that “any supplemental O_2_” applies to any supplemental oxygen the patient is receiving. It does not apply to patients who are on masks through which only air is being supplied (air delivery possible through tracheostomy, bilevel positive airway pressure or continuous positive airway pressure, for example).

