### Study Design

The study is a single-center, prospective observational study to investigate the agreement of the RespiraSense device compared with (1) other device measurements (capnography, ECG) and (2) the current standard measurement of RR (manual counting by a trained HCP). The different methods will be employed concurrently on the same participant as part of a single study visit.

Once participants have provided consent, the following baseline data will be collected:

Demographics (age, sex)Height, weight (to calculate body mass index)Skin assessment at RespiraSense device attachment site (color, texture, uniformity of appearance, integrity). It will also be confirmed that the skin has no discoloration or rash, epidermal loss, blistering, edema, tears, maceration or folliculitisOxygen saturation and pulse oximetry

Participants will be asked to wear a hospital gown and be positioned on an examination couch in the simulation suite. The RespiraSense device, a nasal cannula, and an ECG will be attached and a video recorder positioned to ensure the viewers of the video experience the same image as the HCP performing manual RR monitoring.

A computer-based metronome will be used to produce a repetitive tone at a set rate, which is played to each participant via headphones. The metronome has been produced for the study by the study sponsor team using Microsoft Visual Basic. The metronome rates will be generated using a random number generator program, and the order of the different rates will vary with each participant to ensure the rates are random. The participants will be asked to begin to inspire when each tone is heard and will be given a 20-second warm-up period during which time they will regulate their breathing pattern to match the rate of the tone they hear. Each participant will be asked to breathe at one value from each of the following categories for 2 minutes:

≤8 breaths per minute9 to 11 breaths per minute12 to 20 breaths per minute21 to 24 breaths per minute25 to 29 breaths per minute30 to 35 breaths per minute

One rate will be randomly generated from within each of the 6 categories. Examples of potential sets are shown in Table 2.

**Table 2 table2:** Examples of possible sets of metronome rates to be used.

Participant	First rate	Second rate	Third rate	Fourth rate	Fifth rate	Sixth rate
Participant A	6	10	23	17	28	32
Participant B	5	14	9	22	31	26
Participant C	11	7	13	21	33	27

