### Statistical Analysis

The primary end point is the RR as measured by multiple methods. The primary objective of the analysis is to examine the agreement between the RespiraSense device and the other measurement methods for this end point. The mean difference between each pair of methods will be calculated with 95% confidence intervals. Variances will be tested for nonequality with an *F* test. The distributions of the differences will be examined with Bland-Altman plots. Limits of agreement (LoAs) and proportions of measurements outside the limits will be compared. If the differences between methods markedly increase with their mean, the analysis will be repeated with a log transformation of the measurements. A secondary analysis of agreement by participant position (45 degree sitting vs other positions) for each pair of methods will be performed using an analysis of variance.

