## Discussion

### Rationale for Study Design

The Evaluation of Agreement of Breathing Rates Measured by a Novel Device, Manual Counting, and Other Techniques Used in Clinical Practice (VENTILATE) study will test the accuracy of the RespiraSense device at the extremes of RR. The selection of randomized RRs from within defined categories allows these abnormal RRs to be compared with normal RRs without introducing variability in the participant or the HCP. Additionally, video recording of the study procedures allows for independent sampling and monitoring of the ability of the HCP to manually count the RR by another HCP.

We chose to use healthy volunteers without underlying cardiopulmonary disease. It was not deemed safe or appropriate to use patients exhibiting extremes of RR in an observational study of this type. It was decided that the safest way to observe the RRs of interest for the study would be for healthy volunteers to consciously breathe at a given rate.

There are multiple points of contact during the screening visit to minimize the chance that participants fail to complete the study procedures. In addition to the standard practice of providing a PIS and allowing the participant time to consider what will be required of them during the study, the participants will also experience one of the higher RRs that they will be asked to perform during the study day. We chose to do this with the aim of reducing the number of participants who are unable to complete all of the study procedures.

Although the risk of harm to study participants is low, further measures will be taken to mitigate these risks. The potential risk of feeling unwell after breathing at high or low RRs will be mitigated by allowing participants to rest for longer than scheduled or to stop the procedure entirely should they feel unable to continue. A clinician will be present throughout the study procedures and will be able to stop the study at their discretion if they feel it is not safe or would be inappropriate to continue.

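### The study is built to test agreement at abnormal breathing rates, but the planned numerical results and the sample size combine all rates, so bias and limits at the extremes are not estimated

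*Protocol article*

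**What the plan says.** **Purpose.** The Background says of the earlier 48-patient investigation that "few abnormal values were recorded in this investigation, and further research is required", and asks whether the device can "accurately measure the RR at values both higher and lower than the normal range". The Rationale for Study Design says that the "study will test the accuracy of the RespiraSense device at the extremes of RR" and that the choice of rates "allows these abnormal RRs to be compared with normal RRs without introducing variability in the participant or the HCP". The Conclusions section repeats the aim of assessing the device at abnormal rates.

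**Design.** Under Study Design there are six categories (≤8, 9-11, 12-20, 21-24, 25-29 and 30-35 breaths/min), and "One rate will be randomly generated from within each of the 6 categories". These six rates are done at 45 degrees. Four more follow in one other position, and their categories are not stated.

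**Analysis.** The Statistical Analysis section says: "The mean difference between each pair of methods will be calculated with 95% confidence intervals". It adds an F test of variances, Bland-Altman plots, and LoAs with the proportion of readings outside them. One contingency depends on rate: "If the differences between methods markedly increase with their mean, the analysis will be repeated with a log transformation of the measurements". The only factor named is position, by analysis of variance.

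**Sample size.** Patient Population Size rests on 300 data sets (30 participants, 10 readings each). Tables 3 and 4 mark the precisions expected after 10% loss, with no split by rate.

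**The concern.** The rate category is the main structural feature of the design, and the comparison of abnormal with normal rates is the stated reason for it. Yet no planned estimate is tied to category. A mean difference over roughly 5 to 35 breaths/min averages over exactly the contrast of interest. If the device over-reads slow breathing and under-reads fast breathing, a plausible pattern for a smoothing or range-limited algorithm, the two errors offset each other in the mean. The same errors inflate the SD of the differences, so the combined LoAs are too wide for the normal range and wrongly centred at both ends. A reader wanting the bias and limits at ≤8 or at 30-35 would not find them among the planned results, and the sample-size section gives no indication of how precise they would be.

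**Working it through.** **1. The protocol's own figures.** Inputs from Patient Population Size: SD 1.79 (against ECG and capnography), SD 2.5 (against the health care professional), 95% confidence.

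- Mean: N = (1.96 × SD / precision)². For SD 1.79 and ±0.25 this is 196.9, so 197. For SD 2.5 and ±0.3 it is 266.8, so 267.
- LoA: N = 3 × (1.96 × SD / precision)². For SD 1.79 and ±0.4 this is 230.8, so 231. For SD 2.5 and ±0.6 it is 200.1, so 201.

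All 14 rows of Table 3 and all 15 rows of Table 4 reproduce. The marked rows are reachable only with 300 × 0.9 = 270 readings, that is, with all rates combined and readings treated as independent.

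**2. What opposite errors do to the combined results.** Assumed, not from the protocol: category midpoints 6.5, 10, 16, 22.5, 27 and 32.5 (mean 19.08), equal numbers per category, and a device reading of 19.08 + 0.8 × (true rate − 19.08). The bias is then −0.2 × (true rate − 19.08).

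| Midpoint | Bias | True limits (SD 1.79) |
|---|---|---|
| 6.5 | +2.52 | −0.99 to 6.03 |
| 10 | +1.82 | −1.69 to 5.33 |
| 16 | +0.62 | −2.89 to 4.13 |
| 22.5 | −0.68 | −4.19 to 2.83 |
| 27 | −1.58 | −5.09 to 1.93 |
| 32.5 | −2.68 | −6.19 to 0.83 |

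- Combined bias = mean of the six = 0.
- Variance of the six biases = 3.36. Combined SD = √(1.79² + 3.36) = 2.56. Combined LoAs = ±1.96 × 2.56 = ±5.02, against ±1.96 × 1.79 = ±3.51 with no bias.
- With SD 2.5: √(6.25 + 3.36) = 3.10, so ±6.08 against ±4.90.

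Limits of −5.0 to +5.0 describe neither the slowest category (−1.0 to 6.0) nor the fastest (−6.2 to 0.8). To give the error a scale from Table 1 of the article: a true 6.5 lies in the band scoring 3, and the expected reading of 9.0 lies in the band scoring 1.

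**3. Does the log step help?** In this example the signed differences fall as the mean rises, so the stated trigger is not met on its ordinary reading. If the step were run anyway, the device/true ratio would still go from 9.02/6.5 = 1.39 at the slow end to 29.82/32.5 = 0.92 at the fast end. A log scale addresses spread that grows with rate; it does not remove a bias that changes sign.

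**4. Precision by category.** At 45 degrees each participant gives one reading per category: 30, or 27 after 10% loss.

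| SD | Mean, n = 27 | Mean, n = 270 | LoA, n = 27 | LoA, n = 270 |
|---|---|---|---|---|
| 1.79 | ±0.68 | ±0.21 | ±1.17 | ±0.37 |
| 2.5 | ±0.94 | ±0.30 | ±1.63 | ±0.52 |

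Formulas: 1.96 × SD/√n and 1.96 × SD × √(3/n). The ratio is √(270/27) = 3.16. The n = 270 columns follow the protocol in ignoring correlation within participants.

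**The case against.** Much of the case on the other side stands.

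- **The log step is not the only provision that bears on rate.** Bland-Altman plots show difference against mean. In the example above, with noise placed in the device reading, the correlation between the two is about −0.64 (SD 1.79) or −0.46 (SD 2.5), which would be visible. If the F test compares the variances of the methods' readings (the text does not say which variances), compressed device readings would probably be flagged: in simulation of the example with independent readings it rejected in over 99% of runs at n = 270 for either SD.
- **A reader might infer that a poor device would be reported as accurate, with zero bias.** The documents do not support that. Only the mean cancels; the LoAs widen from ±3.5 to ±5.0 and would be reported too.
- **A reader might also point to SD growing with rate.** That is the case the log step is designed for, so it is not evidence of a gap.
- **Exact cancellation is a constructed case.** It needs the error to cross zero at the average rate and the categories to be balanced, and the categories of the four extra rates are not stated. With +2 in the two low categories, 0 in one and −2 in three, the combined bias is −0.33.
- **The formal primary objective is overall agreement,** across a range of set rates, and no listed secondary objective is agreement by category. It would therefore go too far to say that the study answers nothing it asks.
- **This is a condensed article.** Combining the rates is inferred from the analysis and sample-size sections; the article does not use the word, and a separate analysis plan could add results by rate.

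What these points do not supply is an estimate of bias or limits at any rate. A plot and a variance test can signal a problem but cannot say how large it is at ≤8 or at 30-35. Nor is this only omitted detail: the article names its one factor (position), fixes its one rate contingency, and justifies its size on precision that requires all rates together.

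**Conclusion.** The point holds in this form: the stated purpose and the six-category design call for agreement by rate, while the planned numerical results are one mean difference and one set of LoAs per pair of methods, and the sample size is justified only for all rates combined. Under the assumed slope of 0.8, biases of +2.5 and −2.7 breaths/min at the two ends would appear as a combined bias of 0 with LoAs of about ±5.0 (SD 1.79) or ±6.1 (SD 2.5). These sizes illustrate the mechanism and do not predict the device's behaviour; they rest on assumed midpoints, equal weights and a constant SD. The precision result needs less: only the protocol's own SDs, formulas and 10% loss. The finding does not extend to saying that a rate-dependent error would go unnoticed, since the plots and perhaps the F test could show it.

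**What to change.** **Statistical Analysis.** Add to the agreement analysis, for each pair of methods, the bias and LoAs in each of the six metronome rate categories, or a regression of the differences on rate with regression-based LoAs. Include a participant random effect, and give the contrast of abnormal with normal (12-20) rates with its 95% confidence interval. Keep the combined LoAs as an overall summary. Category-specific residual variances are one acceptable option, not a requirement. The log step may stay for spread that grows with rate, but should not be relied on for a bias that changes with rate.

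**Patient Population Size.** State the per-category precision for the 45-degree block with 27 readings: about ±0.68 (SD 1.79) or ±0.94 (SD 2.5) for the mean, and ±1.17 or ±1.63 for the LoA.

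**Cost.** Wording and a little more analysis. The categories are already part of the data collection and recruitment has not started, so no new data are needed. The drawback is intervals about 3.2 times wider per category than for all 270 readings, which should be stated openly.

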### Patient Population Size

We expect to have statistically significant data following the collection of 300 data sets (10 distinct measurements taken from 30 unique participants). This is based on statistical analysis of previous studies.

The precision of the mean and precision of the LoAs depend on the standard deviation of the differences. We use the value of 1.79 breaths per minute as the standard deviation reported in the Lee study [12] for comparison of RespiraSense and ECG and the same value for the comparison of RespiraSense with end-tidal capnography, this being regarded as more accurate than ECG. For comparison with an HCP, we use the value of 2.5 breaths per minute, also from the Lee study.

Table 3 shows the number required for different precisions of the mean difference using 95% confidence intervals. Table 4 shows the number required for different precisions of the LoA.

**Table 3 table3:** Precision of mean at 95% confidence interval.

Breaths per minute	Precision of the mean	Standard error of the mean	N
1.79	1	0.51	13
1.79	0.5	0.26	50
1.79	0.4	0.2	77
1.79	0.3	0.15	137
1.79	0.25	0.13	197^a^
1.79	0.2	0.1	308
1.79	0.1	0.05	1231
2.5	1	0.51	25
2.5	0.5	0.26	97
2.5	0.4	0.2	151
2.5	0.3	0.15	267^a^
2.5	0.25	0.13	385
2.5	0.2	0.1	601
2.5	0.1	0.05	2401

^a^Precisions to be expected if 30 participants provide 10 data points each, allowing for a 10% loss of data.

**Table 4 table4:** Precision of limits of agreement at 95% confidence interval.

Breaths per minute	Precision of LoA^a^	Standard error of LoA	N
1.79	1	0.51	37
1.79	0.5	0.26	148
1.79	0.4	0.2	231^b^
1.79	0.3	0.15	411
1.79	0.25	0.13	591
1.79	0.2	0.1	924
1.79	0.1	0.05	3693
2.5	1	0.51	73
2.5	0.6	0.31	201^b^
2.5	0.5	0.26	289
2.5	0.4	0.2	451
2.5	0.3	0.15	801
2.5	0.25	0.13	1153
2.5	0.2	0.1	1801
2.5	0.1	0.05	7203

^a^LoA: limits of agreement.

^b^Precisions to be expected if 30 participants provide 10 data points each, allowing for a 10% loss of data.

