### Conclusions

The VENTILATE study will provide further validation of the use of the RespiraSense device in subjects with abnormal respiratory rates. It will assess the device’s ability to measure abnormal RRs and compare with multiple other techniques used in various aspects of clinical practice. The results provided will help to guide the usefulness of the device in clinical practice in the future.

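### The share of readings outside the study's own limits of agreement is about 5% for every method pair, so comparing it says nothing about which pair agrees better

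*Protocol article*

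**What the plan says.** The Statistical Analysis section sets the aim: "The primary objective of the analysis is to examine the agreement between the RespiraSense device and the other measurement methods for this end point". For each pair of methods it plans the mean difference with a 95% confidence interval and an F test of the variances. It continues: "The distributions of the differences will be examined with Bland-Altman plots". The next sentence is the one at issue: "Limits of agreement (LoAs) and proportions of measurements outside the limits will be compared". A log transformation follows if the differences grow markedly with the mean.

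The section names no limits other than the LoAs. Patient Population Size treats these as quantities estimated from the data: "The precision of the mean and precision of the LoAs depend on the standard deviation of the differences". Table 4 accordingly gives them standard errors. The article states no maximum acceptable difference between methods.

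**The concern.** A proportion of readings outside limits looks like a measure of agreement: the fewer outside, the better the methods agree. That holds when the limits are fixed from outside the data. It does not hold when each pair's limits are built from that pair's own differences. A pair that agrees poorly gets wider limits, and much the same fraction of its readings lies beyond them.

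The stake is interpretation. A reader who sees about 5% outside for capnography, ECG and manual counting alike could conclude that RespiraSense agrees equally well with all three, even where the LoAs differ widely. A device with occasional gross errors could even look better on this comparison.

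**Working it through.** **Inputs.** From Patient Population Size:
- SD of differences against ECG, also used for capnography: "We use the value of 1.79 breaths per minute as the standard deviation".
- SD against manual counting: "For comparison with an HCP, we use the value of 2.5 breaths per minute".
- 30 participants × 10 readings = 300, less the 10% loss allowed for in the table footnotes = 270.

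The LoA multiplier is not stated. The usual 1.96 is assumed; any fixed multiplier gives the same invariance at a different percentage.

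**Step 1: the plan's own figures.** The article gives no figure for the proportion outside, but its precision tables show how it treats the LoAs.
- Mean: N = (1.96 × SD / precision)². SD 1.79, ±0.25: (3.508/0.25)² = 196.9, so 197. SD 2.5, ±0.3: (4.9/0.3)² = 266.8, so 267.
- LoA: N = 3 × (1.96 × SD / precision)². SD 1.79, ±0.4: 3 × (3.508/0.4)² = 230.8, so 231. SD 2.5, ±0.6: 3 × (4.9/0.6)² = 200.1, so 201.

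All 29 rows of Tables 3 and 4 reproduce. The LoA formula is the one for limits estimated from the sample, which confirms that the LoAs are not a preset tolerance.

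**Step 2: share outside a pair's own limits.** For normal differences D with mean μ and SD σ:

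P(|D − μ| > 1.96σ) = 2 × (1 − Φ(1.96)) = 0.050.

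Both μ and σ cancel. At SD 1.79 the limits are the mean ± 3.51 (width 7.0); at SD 2.5 they are the mean ± 4.90 (width 9.8). The share is 5.0% in both.

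**Step 3: simulation.** 4,000 studies of 270 differences, each study using its own mean ± 1.96 SD. Bias and SD are in breaths per minute; values other than 1.79 and 2.5 are assumptions to show the range.

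| Bias | SD | Mean LoA width | Mean share outside own LoA |
|---|---|---|---|
| 0 | 0.5 | 2.0 | 5.0% |
| 0 | 1.79 | 7.0 | 4.9% |
| 0 | 2.5 | 9.8 | 5.0% |
| 0 | 5 | 19.6 | 4.9% |
| 0 | 10 | 39.2 | 4.9% |
| 5 | 1.79 | 7.0 | 4.9% |
| 5 | 10 | 39.2 | 5.0% |

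In every row the central 95% of studies lay between 3.3% and 6.7%, so differences of that order between pairs can arise by chance alone. Clustering within participants (assumed intraclass correlation 0.5, SD 2.5) gave 4.9%.

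**Step 4: what does move the share.** Shape moves it: 0% for uniform, 6.3% for Laplace and 5.3% for exponential differences. Occasional gross errors added to a base SD of 1.79 lower it:
- 5% of readings at 5 times the SD: 3.4% outside, while the LoA width rises from 7.0 to 10.3.
- 2% of readings at 10 times the SD: 2.1% outside, while the width rises to 11.8.

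Here agreement worsens and the proportion improves.

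**Step 5: a common fixed limit, for contrast.** The share is 2 × (1 − Φ(limit/SD)) with zero bias. The limits are illustrative; the article gives none.
- ±3: 3/1.79 = 1.676 gives 9.4%; 3/2.5 = 1.2 gives 23.0%.
- ±2: 2/1.79 = 1.117 gives 26.4%; 2/2.5 = 0.8 gives 42.4%.

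A bias of 5 at SD 1.79, invisible in Step 3, puts 86.8% of readings beyond ±3.

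**The case against.** **The proportion is one item among several.** The same sentence compares the LoAs themselves, whose width tracks agreement directly, and mean differences with confidence intervals are also planned. This stands. A reader might infer that the analysis as a whole cannot tell good agreement from poor. The document does not support that: removing the proportion would leave the bias and LoA estimates unchanged.

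**It may be meant as a distribution check.** The sentence follows the one on Bland-Altman plots, and the share does respond to shape and outliers. As a check it has a use. But it is announced as something to be compared alongside the LoAs, under an objective of agreement, with no mention of a check.

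**A common limit may be meant.** The comparison would then be informative: limits of ±3.51 (1.96 × 1.79) applied to SD 2.5 with zero bias leave 16.1% outside. The text states no such limit.

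**An acceptability limit may sit in a document not shown.** This is fair. A condensed article can leave that limit to the full protocol or analysis plan, so its absence alone is not counted as a fault. The point rests on a comparison that the article does state.

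**Two further inferences go too far.** One is that statistical significance is the only expectation set, from "We expect to have statistically significant data following the collection of 300 data sets". The footnotes to Tables 3 and 4 mark expected precisions: ±0.25 and ±0.3 for the mean, ±0.4 and ±0.6 for the LoAs. The other is that the Conclusions claim a pass by saying the study "will provide further validation of the use of the RespiraSense device in subjects with abnormal respiratory rates". That is prospective wording and sets no pass or fail rule.

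**Conclusion.** The point holds for the proportion only. Counted against limits built from the same differences, it is expected to be about 5% at both planning SDs and at any other SD or bias. It cannot rank the method pairs on agreement, and it can fall when gross errors make agreement worse. The figure of 5% assumes roughly normal differences and a multiplier of 1.96; departures from normality shift it for reasons of shape. The conclusion also takes the limits to be each pair's own LoAs, the only ones named. Mean differences, LoA widths and the sample-size tables are unaffected. The wording should be changed before recruitment, but the primary estimates are sound on this point.

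**What to change.** In the Statistical Analysis section:

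1. Replace the comparison of proportions outside the LoAs with the proportion of paired readings that differ by more than one common limit, the same for every pair. The clinical team fixes this limit before data collection. The ±2 and ±3 above are arithmetic examples, not proposals.
2. Give that proportion a confidence interval that allows for the repeated readings per participant, for example by resampling whole participants or using cluster-robust standard errors.
3. Read each LoA, with its confidence interval, against the same limit. If the log transformation is used, convert the LoAs back to breaths per minute at stated rates first; the proportion is counted on the original scale either way.
4. Keep the share outside the study's own LoAs, if at all, only as a labelled check of distribution shape and outliers.

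Agreement by the respiratory-rate bands of Table 1 could be added as an optional description. It should carry no weight in the conclusion, because the metronome scheme draws a rate from every category and edge rates are common by design: two of the three whole rates in 9 to 11, and two of the four in 21 to 24. A one-breath difference there can change the band.

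The cost is one clinical decision before the study and a few lines of analysis text. No extra participants, visits or measurements are needed, and the article reports that recruitment had not begun.
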